### 1.6 Data Safety Monitoring Committee

A data safety committee of two persons with experience in clinical research and biostatistics who are not part of the investigators or future authors of the scientific publication will monitor the safety of data and of the study; during the interim analyses (approximatively after one and two years into the study).

### 1.7 Any other relevant Committee, Person, Organisation, Institution

The study takes place at the Balgrist University Hospital.

## 2. ETHICAL AND REGULATORY ASPECTS

The decision of the Competent Ethics Committee (CEC) concerning the conduct of the study will be made in writing to the Sponsor-Investigator before commencement of this study. The clinical study can only begin once approval from the CEC has been received. Any requirements imposed by the authorities shall be implemented.

### 2.1 Study registration

The study will be registered at <http://www.clinicaltrials.gov> and <http://www.snctp.ch>.

### 2.2 Categorization of study

Category A. The investigational products used in this study are already authorized in Switzerland for the prevention of surgical sites infections. The indication and the dosage are used in accordance with the product information and international guidelines. There will be no placebo.

### 2.3 Competent Ethics Committee (CEC)

The principal investigator ensures that approval from an appropriately constituted Competent Ethics Committee (CEC) is sought for this clinical study.

The reporting duties such as all changes in research activity, all unanticipated problems involving risks to humans and planned or premature study end and the allowed time frame are respected by this study. The study protocol will not be changed without prior Sponsor and CEC approval, except when it's necessary to eliminate apparent immediate hazards to study participants.

Premature study end or interruption of the study is reported within 15 days. The regular end of the study is reported to the CEC within 90 days, the final study report shall be submitted within one year after study end. Amendments are reported according to chapter 2.10.

### 2.4 Competent Authorities (CA)

CA (*swissmedic*) approval is only necessary for category B and C studies. Category A studies do not require CA approval. The CA is entitled to carry out inspections of all clinical trials.

### 2.5 Ethical Conduct of the Study

The study will be carried out in accordance to the protocol and with principles enunciated in the current version of the Declaration of Helsinki, the guidelines of Good Clinical Practice (GCP) issued by ICH, the Swiss Law and Swiss regulatory authority's requirements. The CEC and regulatory authorities will receive annual safety and interim reports and will be informed about study stop/end in agreement with local requirements.

### 2.6 Declaration of interest

No conflict of interest compromises the professional judgement of our investigators and the other involved people in conducting and reviewing this study. Their objectivity is not influenced in any way (e.g. independence, intellectual, financial, proprietary) or through any party.

However, Schülke GmbH supports the Trial with an unconditional grant (third party funding) to pay a minor part of the salary of the study nurse(s) and will provide the decolonization sets free of charge and for exclusive use in the study. Schülke GmbH will not have access to the individual non-anonymized data and will not interfere with the scientific publication of the final study results according to the terms specified in the contract of the clinical investigation.

### 2.7 Patient Information and Informed Consent

For the participation in the study, patients will be recruited/preselected by any of the investigators of the study. If patients match the inclusion criteria and do not meet any exclusion criterion, they will be informed by one of the study investigators, about the study, its nature, purpose, procedures involved, expected duration, participating investigators, potential risks and benefits and any potential discomfort the study could entail, during post-surgery visit when an orthopedic infection is diagnosed. Each participant will be informed that the participation in the study is completely voluntary and that he/she may withdraw from the study at any time and that withdrawal of consent will not affect his/her medical assistance and treatment in the future. No further screening requirements (other than the in- and exclusion criteria) exist.

All participants will be provided with a participant information sheet and informed consent form describing the study and entailing sufficient information for the participant to make an informed decision about their willingness to participate in the study. The patient information sheet and the consent form will be submitted to the CEC to be reviewed and approved. The information sheet provides the possibility to read through the study concept again and enables the patient to rethink the study participation without being pressured into deciding. If the participant decides to take part in the study, he/she will be asked to date and sign the informed consent form. The potential participant will be requested to read through the consent form and the information sheet carefully and to clarify any misunderstandings before signing. Once the patient dates and sign the informed consent form, one of the investigators will also date and sign the aforementioned document. The participant will be given a copy of the signed document. The original signed informed consent form will be retained as part of the study records.

The formal consent of a participant, using the approved consent form, must be obtained before the

participant is submitted to any study specific procedures.

The collection of the general consents for further use of health-related personal data and biological material is a standard at UKB. It is not study-specific.

## **2.8 Participant privacy and confidentiality**

The investigators affirm and uphold the principle of the participant's right to privacy and that they shall comply with applicable privacy laws. Especially, anonymity of the participants shall be guaranteed when presenting the data at scientific meetings or publishing them in scientific journals.

Individual subject medical information obtained as a result of this study is considered confidential and disclosure to third parties is prohibited. Subject confidentiality will be further ensured by utilising subject identification code numbers to correspond to treatment data in the computer files.

For data verification purposes, authorised representatives of the Sponsor (-Investigator), a competent authority (e.g. *Swissmedic*), or an ethics committee may require direct access to parts of the medical records relevant to the study, including participants' medical history.

## **2.9 Early termination of the study**

The Sponsor-Investigators may terminate the study prematurely according to certain circumstances, for example:

- ethical concerns,
- insufficient participant recruitment,
- when the safety of the participants is doubtful or at risk, respectively,
- alterations in accepted clinical practice that make the continuation of a clinical trial unwise,
- early evidence of benefit or harm of the experimental intervention, e.g. based on interim analyses

## **2.10 Protocol amendments**

Substantial amendments are only implemented after approval of the CEC.

Under emergency circumstances, deviations from the protocol to protect the rights, safety and well-being of human subjects may proceed without prior approval of the CEC. Such deviations shall be documented and reported to the CEC as soon as possible.

All non-substantial amendments are communicated to the CEC within the Annual Safety Report (ASR).

As substantial Amendments Count:

- a) Changes, which affect security and health of the participants or their rights and duties.
- b) Changes of the study protocol, due to new scientific findings, which affect study arrangement, study methods, objectives or statistical analysis.
- c) Changes of the study location or inclusion of an additional study location.
- d) Personnel changes, such as change of the sponsor-investigator.

# **3. BACKGROUND AND RATIONALE**

## **3.1 Background Rationale**

The general decolonization of the human body surface and, of adjacent pathogen reservoirs such as the nose, by industrial antiseptic agents, before elective surgery is recommended by the World Health Organization (WHO) for the risk reduction of superficial and deep surgical site infection (SSI) in many surgical disciplines. Such a decolonization is regarded as evidence-based in the majority of randomized and before-after trials since two decades, although negative studies also exist.

In the orthopedic field, this decolonization is likely to be more effective in elective patients with a proven body colonization of *Staphylococcus aureus*, in orthopedic patients with an inherent high risk for SSI, for which the majority of future SSI pathogens are skin commensals and *S. aureus*. These (eventual and future) pathogens of SSI are accessible to the topical agents during the index surgery, if the patients are well instructed and know how to decolonize themselves.

In contrast, this pre-surgical decolonization is only a supplementary measure in the bundle of all combined efforts to prevent revision surgery for infection. Its individual power is limited for young, healthy individuals, for SSIs caused by pathogens from the internal body sites (intestinal, urinary, gynecologic regions), infections acquired on the surgical ward, and in settings with less specialized surgeries and a low volume of surgical experience. Hence, in trials including all patients (or only those carrying *S. aureus*), the beneficial effect of decolonization can be diluted and provoke an additional costly and cumbersome organizational procedure for the majority of patients with low to moderate SSI risks. Moreover, many surgical site infections in orthopedic surgery, especially in implant-related surgery, are more due to coagulase-negative staphylococci (CoNS) than for *S. aureus*. The hallmark of the CoNS group is *S. epidermidis* with approximately 70% resistance (in Switzerland) to standard prophylactic antibiotic agents. As *S. epidermidis* is part of the normal human flora, typically the skin flora, and, only becomes pathogenic under certain conditions, a screening for this microorganism is not feasible in common practice. while the prophylaxis-resistant part of all orthopedic SSI pathogens is at 30-50%.

In this single-center, prospective, randomized, and controlled superiority trial, which is planned over a period of two years, we target on an orthopedic patient population with an elevated risk for revision surgery and SSI (considering our recommendations in the section “inclusion/exclusion criteria”; independently of a known body carriage for *S. aureus*. Academically and clinically, we will gain insight in the performance of decolonization for a patient population at particular risk of postoperative complications, where every effort to prevent infection is of importance.

### 3.2 Investigational Product and Indication

This study will be performed with an existing “set” manufactured by Schülke & Mayr GmbH. The “set” was placed on the market in 2016. The distribution of octenisan® Set largely streamlines and facilitates the organizational application and compliance efforts of the study. The active substance is octenidine dihydrochloride (Appendix 1). The questionnaire is designed and validated by the Investigators at the Balgrist (Appendix 2).

#### 3.2.1 Study definitions

An orthopedic infection for this trial is the microbiological evidence of bacteria in at least two intraoperative tissue samples together with radiological (osteomyelitis, collections, inflammation) and/or clinical evidence of infection (pus, discharge, sinus tracts, rubor, calor, pain). Histological proof is facultative for this study. Implants are defined as any implants except for transient wires or fixator pins. A wound problem is any unplanned post-surgical wound pathology leading to surgical revision. Remission of infection is the absence of clinical and/or radiological and/or laboratory signs of (former) infection after the minimal follow-up time of 1 year for implant -related surgery with implants left in place; or two months for implant-free surgery (including surgery when all implants have been removed)..

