The duration of pre-surgical decolonization is planned to be five days. However, when this pre-surgical time period is too short, the decolonization may also start at least 3 days before surgery and be continued up to 2 days post-surgery. During the post-surgery application, the patient will be washed with water and octenisan® by their treating nurses. The patient will also return the empty/used set and answer to a short questionnaire during their hospital stay. The study team will recuperate the questionnaire during hospitalization. We renounce on routine microbiological assessments of skin colonization, but the hospital's infection control can demand it for other reasons regarding infection control. Hence, skin colonization data will only be available for some selected patients that are screened for body carriage of antibiotic-resistant pathogens, according to the infection control recommendations in Switzerland.

There will be a Monitoring at study start, the interim analysis and at the end.

The primary study outcomes are unplanned revision surgery for SSI and wound problems at 42 days for all surgeries; or 1 year in case of an implant-related surgery. Secondary objectives are other unplanned revision surgeries for non-SSI reasons, all adverse events, as well as patient's subjective impression of the decolonization.

The treatment period includes the following daily study visits:

- Visit 1 - Enrollment (Day 1)
- End-of-Treatment (EOT) -Visit is the Day of Surgery or Day 1-2 after surgery
- Test-of-Cure-Visit (TOC) (clinical surgical control) - Day 42 (+/- 14 days)
- Further follow-up (eventually by phone call) for implant-related surgery - 1 year (+/- 2 months)

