## 4. STUDY OBJECTIVES

To reduce the incidence of SSI (and other unplanned postoperative wound revisions) in a highly selected patient population with an elevated risk for SSI. To show the safety and all potential (any) adverse events observed during the decolonization period and during the hospitalization for surgery.

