## 5. STUDY OUTCOMES

### Primary outcomes:

- Remission (and inversely superficial or deep-space SSI and revision surgeries for non-infected wound problems; composite primary outcome) at 6 weeks (and/or a 1 year for surgeries with implant)

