### 9. STUDY ASSESSMENTS

#### 9.1 Assessment of primary outcome

Judged by local wound healing (healed vs delayed wound healing according to Reference). The wound healing will be assessed visually by orthopaedic surgeons. Wound nurses and the study investigators may help in the assessment of wound problems, but in case of doubtful cases, the opinion of the treating physician will dominate the decision upon the presence or absence of wound problems and/or infection.

Persistent postsurgical pain, serum laboratory markers, or the patient's subjective wound feelings will not serve as objective criteria for wound healing (or in the contrary, wound discharge and dehiscence). A wound problem solely due to stitches and localized suture problems will not count as a wound problem. A keloid or altered pigment features will not be counted as a problem in this trial. Remission is defined as the absence of any problems and as the absence of any clinical signs of infection.

The primary outcome will be assessed on both, the Intention-to-treat and the per-protocol populations.

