##### **9.2.3 Visit 3 (Test-of-Cure)**

Every effort will be made to ensure that final efficacy assessments (i.e., primary outcome data) are available for all subjects. As all our study visits are part of the routine surgical and postsurgical assessments, we do not expect major drop-out rates; or drop out in very exceptional situations (e.g. transfer to another service because of stroke, non-infectious postsurgical fatalities, etc.) Outpatients should return to the clinic (assessments can be performed in the hospital for inpatients), where the following assessments will be performed:

1. Assess anamnestically all past adverse events of surgery, the hospitalization and decolonization
2. Record clinical and microbiological infection and its treatment (if any)

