### 11.3 Planned Analyses

All analyses will be performed for the entire study population. In a second step, all analyses will be separately performed according to subgroups of patients, based on the type of orthopaedic surgical procedure (e.g. arthroplasties, implant-related surgeries, etc.). We will use descriptive statistics and will perform group comparisons (using the Pearson- $\chi^2$ -test, the Fischer-exact-test, or the Wilcoxon-ranksum-test), as appropriate. We will also perform composite (SSI and wound problems) and separate (SSI or wound problems) multivariate analysis using a Cox regression model targeting the co-primary outcome variables. For the primary outcome parameter, univariable and multivariable results will be computed using a Cox regression analysis. Variables with a  $p$  value  $\leq 0.2$  in univariate analysis will be included in a stepwise forward selection process for multivariate analysis. Key variables will be checked for co-linearity and interaction. The number of variables in the final model is limited to the ratio of 1 variable to 5 to 8 outcome events. The significance level is  $p \leq 0.05$  (two-tailed).

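### Remission, the primary outcome, is defined both as a state at the end of follow-up and as the absence of any SSI or wound revision, and the protocol does not say which governs

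*Protocol*

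**What the plan says.** The protocol describes the primary outcome in several places.

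- **Section 5** (repeated in the Synopsis under Outcome(s)): "Remission (and inversely superficial or deep-space SSI and revision surgeries for non-infected wound problems; composite primary outcome) at 6 weeks", and/or at 1 year for surgery with an implant. Here remission is the complement of an SSI or wound revision.
- **Section 3.2.1**: "Remission of infection is the absence of clinical and/or radiological and/or laboratory signs of (former) infection after the minimal follow-up time of 1 year" for surgery with implants left in place, "or two months for implant-free surgery (including surgery when all implants have been removed"). This is a condition read at the end of follow-up, and the word 'former' presupposes that an infection has occurred.
- **Section 9.1**: "Remission is defined as the absence of any problems and as the absence of any clinical signs of infection". No time window is attached.
- **Synopsis, Study Conduct**: "The primary study outcomes are unplanned revision surgery for SSI and wound problems at 42 days for all surgeries", or 1 year after implant-related surgery. This version counts revisions.
- **Section 4**: the objective is "To reduce the incidence of SSI (and other unplanned postoperative wound revisions) in a highly selected patient population with an elevated risk for SSI".
- **Sections 11.1 and 11.2**: the hypothesis concerns surgical revisions, 10% without and 5% with decolonization. The trial is sized on event-free surgeries.
- **Section 11.3**: "For the primary outcome parameter, univariable and multivariable results will be computed using a Cox regression analysis".

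On data capture, Visit 3 includes the item "Record clinical and microbiological infection and its treatment (if any"), and section 9.2.4 repeats it for the 1-year follow-up.

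**The concern.** A prevention trial asks whether an SSI or wound revision ever happened in the window. Section 3.2.1 answers another question: whether signs of infection are still present when follow-up closes. An implant patient with a deep SSI in week 3 who is treated and has no signs at 1 year meets the 3.2.1 definition of remission. The same patient has had an SSI, so is a failure under section 5. Success and failure are then not complements.

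The trial is unblinded, and section 9.1 lets the treating physician's opinion decide doubtful cases. An unsettled rule for resolved events therefore leaves primary-outcome scoring to people who may know the arm. A state read at one visit also supplies no onset time for the planned Cox model. If cleared SSIs were scored as successes, the event count would fall below the one used for the sample size.

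**Working it through.** **Step 1. One patient under each definition.** Take the implant patient with a deep SSI in week 3, treated, without signs at 1 year.

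| Place in the protocol | What it counts | Score |
|---|---|---|
| 3.2.1 | Signs absent after 1 year | Remission |
| 9.1 | No problems, no clinical signs, time not stated | Either |
| 5 and Synopsis, Outcome(s) | Inverse of SSI or wound revision | Failure |
| Synopsis, Study Conduct | Unplanned revision for SSI or wound problem | Failure if revised |
| 4 | Incidence of SSI and wound revisions | Failure |
| 11.1 | Surgical revisions | Failure if revised |
| 11.2 | Event-free surgeries | Failure |
| 11.3 | Cox model on the primary outcome | Event with an onset time |

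No sentence ranks these, and none says that a resolved event remains an event. Section 3.2.1 also uses two months for implant-free surgery, where section 5 and Visit 3 use 6 weeks (day 42).

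**Step 2. Reproduce the stated sample size.** Inputs: 10% and 5% events (11.1, 11.2), 80% power (11.2), two-sided 0.05 (11.3), 1:1 allocation (6.2.1). With mean rate 0.075:

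n = [1.960·√(2·0.075·0.925) + 0.842·√(0.09 + 0.0475)]² / 0.05² = 434.4, so 435 per arm.

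With continuity correction: (434.4/4)·[1 + √(1 + 4/(434.4·0.05))]² = 473.6, so 474 per arm. This matches the protocol exactly. The sample size is not in dispute.

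**Step 3. Consequence if the state rule were used.** Let m be the share of composite events cleared and scored as remission. The documents give no value, so m is assumed and taken as equal in both arms. The rates become p₁ = 0.10(1−m) and p₂ = 0.05(1−m). With mean rate p̄ and n = 500 per arm:

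power = Φ{[p₁ − p₂ − 1.960·√(2p̄(1−p̄)/n)] / √([p₁(1−p₁) + p₂(1−p₂)]/n)}.

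For the continuity-corrected version, subtract 1/n from p₁ − p₂.

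- m = 0: (0.05 − 1.960·0.01666)/0.01658 = 1.046, power 85%.
- m = 0.20: (0.04 − 1.960·0.01502)/0.01497 = 0.706, power 76%.

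| m (assumed) | Rates | Expected events per 500 | Power, uncorrected | Power, corrected |
|---|---|---|---|---|
| 0 | 10% vs 5% | 50 vs 25 | 85% | 82% |
| 10% | 9% vs 4.5% | 45 vs 22.5 | 81% | 77% |
| 20% | 8% vs 4% | 40 vs 20 | 76% | 72% |
| 30% | 7% vs 3.5% | 35 vs 17.5 | 70% | 65% |
| 50% | 5% vs 2.5% | 25 vs 12.5 | 55% | 48% |

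Solving power = 80% gives m of about 12% uncorrected and about 5% corrected.

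**Step 4. Under the occurrence rule.** m is 0 by definition. The planned rates stand, and 500 per arm gives 85% (82% corrected).

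**The case against.** The best defence is that the protocol mostly treats occurrence as the failure. Section 5 states the inverse outright. The Study Conduct text, the hypothesis, the sizing and the Cox model all point the same way. Section 11.2 also bars re-inclusion of a patient who has been infected or has had a wound problem, so occurrence is a lasting status there. Section 3.2.1 defines remission of infection, and nothing says that this governs the primary outcome. All of this stands, and it makes occurrence the likely intention.

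It also rules out several stronger readings that a reader might infer:

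- *That a cleared SSI definitely counts as a success, so the trial measures cure.* The documents conflict on this; they do not settle it.
- *That 3.2.1 turns a healed, non-infected wound revision into remission.* Its remission wording covers infection only, and the same section defines a wound problem as one that leads to surgical revision, which is an event.
- *That a superficial SSI in an implant-free patient, healed by day 42, is remission under 3.2.1.* That section reads at two months, so the example mixes two definitions.
- *That early events are the particular target of decolonization.* The protocol does not say so, and it follows implant surgery for 1 year.

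The power table has a limit too. It applies m to the whole composite, whereas 3.2.1 could clear only the SSI part.

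What the defence does not supply is a sentence saying which definition governs, or how a resolved SSI is scored. Likely intention is not a rule, and the two explicit definitions of remission, in 3.2.1 and 9.1, are the ones that do not state occurrence.

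**Conclusion.** The point holds as an unresolved contradiction in the primary outcome. A treated and cleared SSI can be scored as success under 3.2.1, and under 9.1 if that is read as a condition at the visit. The same SSI is a failure under section 5, the objective and the sizing. It should be settled before outcomes are scored, because this is the primary variable of an unblinded trial.

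The size is conditional. It is zero if occurrence is the rule. If the state rule were applied, power would drop below the planned 80% once about 12% of composite events were cleared (about 5% on the continuity-corrected basis that reproduces 474). Both thresholds assume the protocol's 10% and 5% rates, 500 episodes per arm and an equal cleared share in each arm. The actual share is unknown.

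**What to change.** In sections 3.2.1, 5 and 9.1, define one primary event: the first superficial or deep SSI, or first unplanned revision for a wound problem, at any time from the index surgery to the end of that patient's outcome window. State that it counts whether or not it has resolved by the visit, and that success means no such event. Bring the Synopsis (Study Conduct and Outcome(s)) into line.

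Delete the remission wording in 3.2.1, or confine it to a descriptive outcome of patients who had an SSI. Reconcile its two months with the 6 weeks (day 42) used elsewhere.

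The cost is an amendment to the text of these sections. Visit 3 and the 1-year follow-up already record infection and its treatment, so no visits are added. The sample size stays as planned, because the 10% and 5% rates already refer to event-free surgeries.
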